#### Side effects

Possible side effects of tDCS are itching or tingling sensation, headache or fatigue and local burns at the position of the electrodes [12].

### Outcome measurements

There will be 3 test moments during the trial: before the start of therapy (T0), after the counselling sessions (T1) and after 84 days (T2). The primary outcome measurements will be assessed at every test moment. However, the secondary outcome measurements will only be assessed at T0 and T2 (Table 2). We are interested in the difference in the amount of change between both groups and the percentage of responders in each group.

**Table 2 Tab2:** Timing of outcome measurements

		T_0_	T_1_	T_2_
Primary outcome measurements	TFI	x	x	x
Secondary outcome measurements	VAS	x	x	x
	HQ	x	x	x
	DS14	x		
	PGIC			x
	Tone audiometry	x		x
	Psychoacoustic measurements	x		x
	ERP	x		x

*DS14* 14-item questionnaire assessing for type D-personality, *HQ* Hyperacusis Questionnaire, *ERP* Event-related Potential, *PGIC* Patient Global Impression of Change, *TFI* Tinnitus Functional Index, *VAS* Visual Analogue Scale

In order to categorise our patient group, all subjects will undergo an audiometric hearing test according to current clinical standards (International Organisation for Standardisation (ISO) 8253–1:2010) with a 2-channel Interacoustics AC 40 (Interacoustics A/S, Middelfart, Denmark) in a soundproof audiometric booth. The TDH-39 headphone is used as transducer to measure air conduction thresholds of frequencies ranging from 125 Hz to 8 kHz. If thresholds exceeding 20 dBHL are found, bone conduction thresholds will be determined within a range of 250 Hz to 4 kHz.

### Primary outcome measurement

#### Tinnitus Functional Index (TFI)

The TFI is a self-reported questionnaire, consisting of 25 questions, which examines the impact of tinnitus on patients’ daily lives. The patient answers each question on a Likert scale ranging from 0 to 10. Questions 1 and 3 are expressed in percentages, and the Likert scale ranges from 0 % to 100 %. The total score is calculated with the mean of all questions. The answers are converted and the total score is expressed as a number between 0 and 100. In addition to the total score, the score of eight subscales can be determined. The subscales are the following: intrusiveness, reduced sense of control, cognitive interference, sleep disturbance, auditory difficulties attributed to tinnitus, interference with relaxation, reduced quality of life and emotional distress [13, 14].

### Secondary outcome measurements

#### Visual Analogue Scale (VAS) of loudness

The patient scores the mean and maximum loudness of their tinnitus on a scale of 0 (absence of tinnitus) to 10 (as loud as possible, cannot be any louder).

#### Hospital Anxiety and Depression Scale (HADS)

The HADS consists of 14 questions that assess anxiety and depression. The patient can choose between four answer options for each question. The score for both components is a summation of the scores of all the questions belonging to the subscale. A result greater than 8 suggests the presence of a depression and/or anxiety disorder [15, 16].

#### Hyperacusis Questionnaire (HQ)

The HQ is a 14-item questionnaire that surveys a patient’s hypersensitivity to sound. There are four answer options for every question: ‘no’, ‘yes a little’, ‘yes quite a lot’ and ‘yes a lot’. A score of 28 is the cut-off for auditory hypersensitivity [17, 18].

#### Patient Global Impression of Change (PGIC)

The PGIC assesses the patient’s perceived improvement in the severity of the tinnitus as a result of the therapy. The patient’s response options are the following: ‘very much improved’, ‘much improved’, ‘minimally improved’, ‘unchanged’, ‘minimally worse’, ‘much worse’ and ‘very much worse’.

#### DS14

The DS14 is a 14-item questionnaire that assesses the presence of a type-D personality. Half the items refer to negative affectivity and the other half refer to social inhibition. A score above or equal to 10 (range 0–28) on both scales classifies a person as a type-D personality [19]. The DS14 will be administered once at baseline before the start of therapy.

#### Psychoacoustic measurements

Psychoacoustic characteristics, such as frequency of tinnitus, loudness of tinnitus and minimal masking level (MML) will be determined. The frequency of tinnitus will be determined by means of frequency matching. The patient may choose between two presented tones or noises until a tone or noise is found that is similar to the patient’s tinnitus. In case of unilateral tinnitus, the contralateral ear is used as the test ear for frequency matching. In case of bilateral tinnitus, the tones will be presented in the ipsilateral ear. Furthermore, the loudness matching will be determined by comparison of the tinnitus to an external 1-kHz pure tone in the ipsilateral ear. Finally, the MML (i.e., the lowest level of broadband noise necessary to mask the tinnitus) will be determined in the ipsilateral ear.

#### ERP

The event-related potential (ERP) is used to assess the processing of sensory information. The ERP component P300 is elicited by the oddball paradigm whereby the patient has to count the number of rare stimuli (2 kHz) that are presented randomly between frequent stimuli (1 kHz) at an intensity of 70 decibels sound pressure level (dBSPL) with a ratio of respectively 20/80 %. The stimuli used is a tone-burst with rise/fall time of 10 ms and a plateau of 30 ms with a stimulus rate of 1.1/s. Silver/Silver Chloride electrodes are placed according to Standard International Electrode System rule 10–20 on the vertex (Cz), frontal (Fpz) and on the ipsilateral mastoid. The Bio-logic Navigator Pro (Natus, Pleasanton, USA) will be used to measure the ERPs.

### Statistical methods

Data will be analysed with SPSS statistical software version 20 (SPSS Inc., Chicago, IL, USA). Descriptive analyses as means and standard deviations will be used to describe the characteristics of the participants. To compare the results of both intervention arms, repeated measures will be computed if the data is normally distributed. If it is not, the data will be logarithmically transformed first. The outcome measurements will be set as dependent variables; the intervention group (sham versus real) and test moment (T0, T1, T2) are the independent variables. The interaction between test moment, intervention group and hearing thresholds on the outcome measurements will also be calculated. The significance level will be set at *p* < 0.05. Furthermore, the percentage of responders with a minimum reduction of 13 points on the TFI will be calculated by descriptive analyses and also the confidence interval of the observed difference.

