### Inclusion and exclusion criteria

The patient must meet specific criteria during consultation with the ENT before inclusion and randomisation. The appropriate examinations will be performed to make sure the patients meet the exclusion and inclusion criteria. During the study, the patient has the right to leave the study at any time. The occurrence of severe adverse events also can lead to discontinuation of the study.

The inclusion criteria are as follows:Duration of (worsening of) tinnitus between 3 months and 4 yearsMinimum age of the patient is 18 years oldMaximum loudness of tinnitus on the Visual Analogue Scale (VAS) ≥ 4Tinnitus Functional Index (TFI) score ≥ 25

A patient is excluded from the study for the following reasons:Pulsatile tinnitusAuditory thresholds > 70 decibels hearing level (dBHL)PregnancyTreatment of psychiatric disorder by a psychiatristPacemaker or defibrillatorAcoustic neuromaHistory of cerebrovascular accidentMénière’s diseaseWhiplashEpilepsyChange of medication use

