### Sample size calculation

Sample size was calculated using Glimmpse 2.0.0, an open source online tool for calculating power and sample size. The selected statistical test was the univariate approach to repeated measures with Geisser-Greenhouse correction with interactions between test moment (T0, T1, T2) and group (real tDCS versus sham tDCS) and the TFI as outcome measurement. A reduction of 13 points is considered the minimum to obtain a meaningful reduction in TFI outcome scores. To measure improvement, the effect size of the TFI is moderate to high [13]. Based on this information, an overall sample size of 24 was needed to reach a desired power of 0.8, assuming a type-I error rate of 0.05 and a standard deviation of 20.

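### The planned group-by-time test on TFI is valid, but it treats baseline as an outcome level and gives no signed arm difference; a baseline-adjusted model with T1 and T2 contrasts would serve the aim better

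*Protocol article*

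**What the plan says.** The Statistical methods section of the protocol article plans a repeated-measures analysis in SPSS in which "the intervention group (sham versus real) and test moment (T0, T1, T2) are the independent variables". Baseline TFI is not named as a covariate; hearing thresholds enter only through an additional interaction. The section names neither the SPSS procedure nor a rule for missing scores.

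The Sample size calculation names the test more closely: the "univariate approach to repeated measures with Geisser-Greenhouse correction with interactions between test moment (T0, T1, T2) and group". It states that "an overall sample size of 24 was needed to reach a desired power of 0.8", with alpha set at 0.05 and the SD taken as 20, and that "A reduction of 13 points is considered the minimum to obtain a meaningful reduction in TFI outcome scores".

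On the question itself, the Outcome measurements section says "We are interested in the difference in the amount of change between both groups", together with responder percentages. The Discussion frames the goal as relief that comes sooner, is greater, or both. TFI is measured at T0, T1 and T2, and no single time point is named as primary. The Inclusion and exclusion criteria section notes that "the patient has the right to leave the study at any time".

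**The concern.** T0 is measured before any treatment, so no arm effect can exist there. Using it as an outcome level amounts to comparing changes from baseline, which is less efficient than adjusting for baseline unless the correlation between visits is very high.

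The interaction F also responds to any departure from parallel profiles. It does not separate a lasting benefit from one that has gone by T2, or benefit from harm. The plan asks how much more one arm changes than the other and whether relief comes sooner. A reader needs arm differences in points at T1 and T2 with intervals, and the article plans none. Its one mention of a confidence interval is attached to the responder percentages.

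In a trial of 24 patients, efficiency and the retention of partly observed patients both matter.

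**Working it through.** **Inputs.** From the Sample size calculation: N = 24, alpha 0.05, SD 20, 13 points. Assumed because the article does not give them: 1:1 allocation (12 per arm), SD 20 for a single score, compound symmetry with correlation ρ, and the pattern of arm differences at (T0, T1, T2). Three patterns are used: sustained (0, 13, 13), growing (0, 6.5, 13) and early-only (0, 13, 0).

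**The plan's own figure.** N = 24 cannot be reproduced from the printed inputs, because ρ and the mean pattern are not given. For the sustained pattern, 80% power at 24 is reached at ρ of about 0.84. So ρ = 0.84 is carried below as the value most favourable to the plan's own figure, beside 0.5 and 0.7.

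**Planned interaction.** Noncentrality λ = (N/4) Σ(d_t − d̄)² / [400(1 − ρ)], with 2 and 44 df (the correction factor is 1 under compound symmetry).
- Sustained: Σ(d_t − d̄)² = 112.67, so λ = 676 / [400(1 − ρ)] = 3.38, 5.63, 10.56 at ρ = 0.5, 0.7, 0.84.
- Early-only: the same sum, hence the same power.
- Growing: the sum is 84.5, so λ = 507 / [400(1 − ρ)] = 4.23 at ρ = 0.7.

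**Baseline-adjusted T2 contrast.** Residual SD = 20√(1 − ρ²) = 17.32, 14.28, 10.85. The standard error is that value times √(4/24), with 21 df. For 13 points the noncentrality is 1.84, 2.23, 2.93.

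**Baseline-adjusted T1/T2 mean.** Residual SD = 20√[(1 + ρ)/2 − ρ²] = 14.14, 12.00, 9.26. For a mean difference of 13 the noncentrality is 2.25, 2.65, 3.44, with 21 df.

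**Baseline-adjusted joint test of T1 and T2.** λ = (N/4) d′S⁻¹d, where S has 400(1 − ρ²) on the diagonal and 400(ρ − ρ²) off it, with 2 and 20 df. For the sustained pattern λ = 2028 / [400(1 + ρ − 2ρ²)] = 5.07, 7.04, 11.82.

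**Power at N = 24:**

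| Pattern, ρ | Planned interaction | Adjusted joint T1/T2 | Adjusted T1/T2 mean | Adjusted T2 only |
|---|---|---|---|---|
| Sustained, 0.5 | 0.34 | 0.45 | 0.57 | 0.42 |
| Sustained, 0.7 | 0.53 | 0.59 | 0.72 | 0.57 |
| Sustained, 0.84 | 0.81 | 0.82 | 0.91 | 0.80 |
| Growing, 0.7 | 0.41 | 0.44 | 0.48 | 0.57 |
| Early-only, 0.7 | 0.53 | 0.52 | 0.24 | 0.05 |

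**Why the gain shrinks.** The variance of a baseline-adjusted score relative to a change score is 400(1 − ρ²) / [800(1 − ρ)] = (1 + ρ)/2, which is 0.75, 0.85 and 0.92 at the three correlations.

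**Validity.** In simulation (4,000 runs per setting, ρ from 0.5 to 0.8) the type I error of the planned test was 0.046 to 0.051.

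**Missing scores (no dropout rate is given).** One incomplete patient is 1/24, about 4% of the sample, if all three scores are required. Losing four of 24 would lower the planned test's power for the sustained pattern at ρ = 0.7 from 0.53 to 0.44.

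**The case against.** The planned test holds its type I error, and the analysis and sizing sections agree with each other. A group-by-time interaction over three visits is a recognised way to ask whether change differs between arms, and the reported arm means would show the direction. All of that stands: this is a point about efficiency and interpretability, not an error.

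Three stronger readings are tempting, and the article does not support them.

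- *The analysis is restricted to complete cases.* It does not say so. The univariate approach is named only for sizing, the SPSS procedure is not named, and a missing-data rule may stand in a document not shown. The need for all three scores is a consequence of one way of running the plan.
- *A T2 contrast is simply more powerful.* It gains for a growing effect, is level with the plan near ρ = 0.84 for a sustained one, and has power 0.05 against 0.53 for an early-only effect at ρ = 0.7.
- *T2 is the question.* The article names no primary time point, and its aim includes faster relief, which a T2-only primary would demote.

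A mixed model is no cure-all either. It keeps partly observed patients only under a missing-at-random assumption, and a patient with T1 but no T2 adds limited information about T2.

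**Conclusion.** The point holds as an improvement worth making. The plan puts a pre-treatment score on the outcome side, leaves it unused as a covariate, and rests on an omnibus test that yields no signed difference in points.

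For a sustained 13-point difference, keeping a joint test but adjusting for baseline adds about 11 points of power at ρ = 0.5, 6 at 0.7 and 1 at 0.84. It costs about 2 points at most for an early-only effect. The T1/T2 mean adds 23, 19 and 10 points for a sustained effect but loses more than half its power against the plan if the benefit is early-only (0.24 against 0.53 at ρ = 0.7). No single choice wins for every pattern, so the choice has to follow the aim.

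These sizes rest on 1:1 allocation, SD 20 per score, compound symmetry and the assumed patterns. The gain in interpretation, a difference in points with an interval at each visit, depends on none of them.

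**What to change.** Analyse TFI at T1 and T2 in a mixed model with arm, visit, arm-by-visit, baseline TFI and baseline-by-visit. Include all randomised patients with a post-baseline score, and state the missing-at-random assumption. Report the arm differences at T1 and T2 in points with 95% CIs.

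Pre-specify one primary result, chosen to match the aim of faster or greater relief:
- the joint T1/T2 arm test, read together with the two signed differences, since a joint test alone gives no direction;
- the average of the T1 and T2 differences; or
- one named time point, with the other secondary or controlled for multiplicity.

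Do not default to T2 alone.

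The change needs no new data, since TFI is already collected at all three visits, and the Trial status section says that no patient had yet been randomised. It costs a few degrees of freedom in a small trial. The sample size paragraph must also be restated for the new primary test, with the assumed correlation and mean pattern given.

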### Sample size calculation

Sample size was calculated using Glimmpse 2.0.0, an open source online tool for calculating power and sample size. The selected statistical test was the univariate approach to repeated measures with Geisser-Greenhouse correction with interactions between test moment (T0, T1, T2) and group (real tDCS versus sham tDCS) and the TFI as outcome measurement. A reduction of 13 points is considered the minimum to obtain a meaningful reduction in TFI outcome scores. To measure improvement, the effect size of the TFI is moderate to high [13]. Based on this information, an overall sample size of 24 was needed to reach a desired power of 0.8, assuming a type-I error rate of 0.05 and a standard deviation of 20.

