## Background

Tinnitus is the perception of sound without the occurrence of a corresponding external sound source. Approximately 25.3 % of the US population experience some tinnitus and 7.9 % suffer from frequent tinnitus [1]. Currently, there is still no treatment that totally eliminates tinnitus in all patients. Therefore, the goal is to change the reaction to tinnitus and thus reduce the impact of tinnitus on the patient’s daily life. The type of counselling that tries to achieve this goal is called Tinnitus Retraining Therapy (TRT). Early studies have shown that 82 % respond positively to TRT [2]. TRT is comprised of two components: counselling and sound enrichment. Counselling is a one-on-one conversation between the patient and the audiologist or counsellor. A family member may be involved at the patient’s request. The counselling is based on the Jastreboff neurophysiological model [3]. Counselling will educate the patient on the working mechanism of the ear and tinnitus and promote adaptive coping behaviours. The second important aspect of TRT is sound enrichment. This can be achieved through a noise masker or even background noise in the environment. Sound enrichment results in partial or complete masking of the tinnitus, allowing the patient to ignore or transfer it to the subconscious. Philips et al. (2010) emphasised the importance of using low-level noise instead of completely masking the tinnitus to achieve down-regulation [4].

Transcranial Direct Current Stimulation (tDCS) is a form of neuromodulation in which a low current is applied to the brain by means of two electrodes: the anode placed on the dysfunctional site and the cathode placed on a ‘silent’ part of the body. Nowadays, mostly bifrontal tDCS is applied in tinnitus patients with the anode and cathode placed on the right and left dorsolateral prefrontal cortex (DLPFC) respectively. However, Martin et al. suggested placing the cathode on the right upper arm and the anode on the left DLPFC to prevent cathode-related inhibitory effects at the cortical site [5]. Research has shown that tDCS can provide temporary relief from tinnitus in 39.5 % of tinnitus patients [6]. In addition, previous studies have shown that tDCS has a beneficial effect on numerical competence [7] and working memory in depressed persons [8]. It also has also been reported beneficial to learning and memory in persons with a brain injury [9].

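### The inputs given do not support the stated power of 0.8 with 24 patients: no between-arm difference or within-patient correlation is stated, and a 13-point difference would need a correlation of about 0.84

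*Protocol article*

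**What the plan says.** The protocol article, Sample size calculation, names the software and the test: the univariate repeated-measures approach with Geisser-Greenhouse correction, for the interaction of group (real or sham tDCS) with test moment (T0, T1, T2), with the TFI as outcome. For the effect it says "A reduction of 13 points is considered the minimum to obtain a meaningful reduction in TFI outcome scores". It adds, citing a source, that the TFI's effect size for measuring improvement is moderate to high. It presents the sample size as following from these statements: "an overall sample size of 24 was needed to reach a desired power of 0.8, assuming a type-I error rate of 0.05". The SD is taken as 20.

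Statistical methods uses the same 13 points as a cut-off for individual patients, in the planned percentage of "responders with a minimum reduction of 13 points on the TFI". Both arms receive Tinnitus Retraining Therapy (TRT). The stated aim is the effect that tDCS adds to it.

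**The concern.** The test concerns a difference between arms in change over time. Its power depends on the arm means at T0, T1 and T2 and on the correlation between a patient's repeated scores. The section gives neither. The 13 points describe how far a score must fall for the fall to be meaningful, which is a within-patient quantity. They are not stated to be the difference between real and sham tDCS. The section also does not say whether SD 20 belongs to single scores or to change.

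The TFI is the only primary outcome, and its interpretation rests on this claim. If 24 patients give much less than 0.8 power for a 13-point added benefit, a non-significant interaction could be read as evidence that tDCS adds nothing when the trial could not settle the question.

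**Working it through.** **Inputs from the document:** total N = 24, two arms, three test moments, SD 20, alpha 0.05, power 0.8, 13 points.

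**Assumptions, because the document does not give them:** 1:1 allocation (12 per arm), SD 20 for single scores, compound symmetry with correlation ρ, no dropout, and 13 points taken as the between-arm difference.

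**Can the plan's figure be reproduced?** Not from the printed inputs alone, since ρ and the arm means are missing. The check is therefore which values would yield 24.

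**Formula.** With d_t the between-arm difference at test moment t and n patients per arm, the interaction F test has

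λ = (n/2) × Σ(d_t − mean d)² / [SD² × (1 − ρ)], df1 = 2, df2 = 2 × (N − 2) = 44.

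The critical F at 0.05 is 3.21. Power 0.8 needs λ of about 10.32.

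**Flat pattern (0, 13, 13).** Mean 8.667; sum of squares 8.667² + 2 × 4.333² = 112.67. So λ = 6 × 112.67 / [400 × (1 − ρ)] = 1.69/(1 − ρ).

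**Linear pattern (0, 6.5, 13).** Sum of squares 2 × 6.5² = 84.5. So λ = 6 × 84.5 / [400 × (1 − ρ)] = 1.2675/(1 − ρ).

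| ρ | λ, flat | Power, flat | λ, linear | Power, linear |
|---|---|---|---|---|
| 0.5 | 3.38 | 0.34 | 2.54 | 0.26 |
| 0.6 | 4.23 | 0.41 | 3.17 | 0.32 |
| 0.7 | 5.63 | 0.53 | 4.23 | 0.41 |
| 0.8 | 8.45 | 0.71 | 6.34 | 0.58 |

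**Correlation needed for 0.8.** Flat: 1 − ρ = 1.69/10.32 = 0.164, so ρ ≈ 0.84. Linear: 1 − ρ = 1.2675/10.32 = 0.123, so ρ ≈ 0.88. At ρ = 0.84 the SD of change would be 20 × √(2 × 0.16) = 11.3 points.

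**Simulation of the Geisser-Greenhouse-corrected test (20,000 runs, flat pattern).** Power 0.32, 0.51 and 0.70 at ρ = 0.5, 0.7 and 0.8, and 0.80 at ρ = 0.84. The approximation is slightly generous.

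**Total N for 0.8 with a 13-point difference.** At ρ = 0.5: 70 (flat) or 94 (linear). At ρ = 0.7: 44 or 58.

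**Detectable difference with N = 24 at power 0.8 (flat).** For a difference D the sum of squares is (2/3)D², so D = √[10.32 × 400 × (1 − ρ) / (6 × 2/3)]. This gives 22.7, 20.3, 17.6 and 14.4 points at ρ = 0.5, 0.6, 0.7 and 0.8.

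**Other readings of the same inputs.**
- A first-order autoregressive correlation needs an adjacent correlation of 0.89 (flat) to 0.92 (linear).
- A two-sided t test on change scores needs ρ = 0.85; a baseline-adjusted variance needs 0.84.
- If SD 20 is the SD of change, a t test with 12 per arm has power 0.33. The usual formula then needs 2 × (1.96 + 0.84)² × 20²/13² ≈ 37.1, so 38 per arm.
- If the arms diverge by 13 points at each step (0, 13, 26), the sum of squares is 338 and λ = 5.07/(1 − ρ). Power at ρ = 0.5 is 0.79 (simulation 0.77), and 0.80 is reached at about ρ = 0.51.

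**The case against.** The strongest reply is that a figure that does not follow from the printed inputs has not been shown to be wrong. The section prints neither a correlation nor arm means, and nothing in the document excludes a correlation of 0.84 or more. The range 0.5 to 0.8 is the reviewer's assumption. Nor does the section say that 13 points was the between-arm difference entered, and the (0, 13, 26) pattern yields 24 at a moderate correlation. The remark that the effect size is moderate to high may also have entered the calculation through a source that cannot be seen here.

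Most of this stands. A reader might infer that the sample size is an arithmetic error; the document does not allow that conclusion. The last pattern deserves less weight. It implies a 26-point difference at T2, twice the only effect stated, with half of it arising after the counselling sessions during which tDCS is given. Nothing in the document supports it.

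Other tempting inferences also fail:
- *A 13-point benefit would more likely than not be missed.* On the flat pattern this holds at correlation 0.5 and 0.6, but not at 0.7 (0.53) or 0.8 (0.71).
- *The 82 % quoted in Background shows that the true difference must be below 13.* That figure counts patients who "respond positively to TRT" in early studies. It is not a TFI change and cannot size the difference between arms.
- *The 24 came from a pooled time effect.* A linear 13-point fall with both arms pooled gives 0.79 at correlation 0.5, but so does the (0, 13, 26) interaction, and the section names the interaction. The match does not identify the origin.
- *Dropout was ignored.* The statement that "the patient has the right to leave the study at any time" is a standard right, and a dropout allowance may sit in the full protocol.

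It could also be said that software inputs are a detail an article may leave out. That does not answer the point: the section does state an effect and presents 24 as following from it, and that effect is not a between-arm quantity.

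**Conclusion.** The concern holds in a limited form. The claim of power 0.8 for the added effect of tDCS is unsupported by the inputs given, but not proven false. If 13 points is the between-arm difference, 24 patients give power of 0.34 to 0.71 over correlations of 0.5 to 0.8 on the flat pattern and 0.26 to 0.58 on the linear one. Reaching 0.8 needs a correlation of about 0.84 or 0.88 respectively, or a between-arm difference well above 13 points. These figures rest on 12 per arm, SD 20 for single scores, compound symmetry and complete data. The arithmetic is firm. What was actually entered in the software is unknown.

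**What to change.** Keep N = 24 and restate the Sample size calculation section:
- Give the between-arm TFI difference assumed at T1 and at T2, the correlation entered, and whether SD 20 refers to single scores or to change.
- Unless the correlation entered was about 0.84 or more, replace the claim of 0.8. Give instead the power for a 13-point between-arm difference over correlations of 0.5 to 0.8 (0.34 to 0.71, flat pattern), or the difference detectable at power 0.8 (about 23 to 14 points).
- State that a non-significant interaction does not by itself exclude a 13-point added benefit.
- Report the between-arm difference in TFI change with its 95% confidence interval. Outcome measurements already names the difference in change as a target, and Statistical methods already mentions a confidence interval for the observed difference, in its sentence on responders.

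The cost is wording and one added reported estimate, with no extra patients. The downside is a less favourable stated power.
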